# A wearable motion capture suit and machine learning predict disease progression in Friedreich's ataxia

---

In the format provided by the  
authors and unedited

**Supplementary Table 1.** Characteristics of the EFACTS study participants included in our analysis. Data is presented as mean (range) or N(%).

|                                          |                         |
|------------------------------------------|-------------------------|
| N                                        | 164                     |
| Women
N (%)                           | 91
(55.5%)           |
| Non-ambulatory
N (%)                  | 31
(19%)             |
| Age at study
entry (in years)         | 46.34
(22 - 76)      |
| Age of onset (in
years)               | 29.26
(18 - 65)      |
| Disease duration
(in years)           | 17.08
(2 - 40)       |
| SARA                                     | 16.81
(1.50-34.00)   |
| SCAFI                                    | -0.05
(-2.46-2.54)   |
| 8MW
(in seconds)                      | 11.24
(3.25-99.00)   |
| 9HPT – Dom.
Hand
(in seconds)      | 50.67
(11.50-289.00) |
| 9HPT – Non-
Dom. Hand
(in seconds) | 56.35
(16.30-248.00) |
| PATA                                     | 21.08
(7.00-39.00)   |
| GAA short
allele repeats              | 352
(43 - 1000)      |
| GAA long
allele repeats               | 787
(150 - 1250)     |

**Supplementary Table 2.** List of suit features from the 8MW task along with their mean and standard error values for the FA patients and control cohorts and p-value of the Kruskal-Wallis one-way ANOVA test between the cohorts. Data are presented as mean (standard deviation). Please note that there are 2 measurements per visit.

| Feature name                                                                | FA patients
mean(std)
(N=62
measurements) | Controls
mean(std)
(N=18
measurements) | p-value     |
|-----------------------------------------------------------------------------|----------------------------------------------------|-------------------------------------------------|-------------|
| Workspace volume                                                            | 12234.84
(1634.98)                              | 7511.11
(1876.85)                            | 5.69E-10    |
| Workspace entropy                                                           | 0.19 (0.04)                                        | 0.1 (0.03)                                      | 1.26E-09    |
| Variability in velocity - hip flexion                                       | 0.13 (0.04)                                        | 0.19 (0.25)                                     | 0.044987291 |
| Variability in velocity - knee rotation                                     | 0.5 (0.13)                                         | 0.42 (0.24)                                     | 0.048814512 |
| Principal component 1 of autocorrelation at first walk cycle                | 2.06 (0.78)                                        | 2.47 (1.57)                                     | 0.019340498 |
| Principal component 2 of autocorrelation at first walk cycle                | -0.68 (0.32)                                       | -0.39 (0.45)                                    | 0.00511391  |
| 1st eigen spectrum values of the channel-delay cross-correlation matrix     | 349.09 (66.48)                                     | 432.28
(136.82)                              | 0.024657373 |
| 5th eigen spectrum values of the channel-delay cross-correlation matrix     | 112.88 (29.36)                                     | 183.36 (69.24)                                  | 5.95E-06    |
| 35th eigen spectrum values of the channel-delay cross-correlation matrix    | 17.96 (3.76)                                       | 13.5 (4.37)                                     | 3.90E-05    |
| Average peak velocity - dominant ankle                                      | 111.27 (35.92)                                     | 157.5 (27.37)                                   | 6.44E-07    |
| Average peak velocity - non-dominant ankle                                  | 109.34 (28.91)                                     | 149.59 (18.57)                                  | 5.39E-07    |
| Average energy per walk cycle of dominant hip flexion velocity              | 121.07 (31.58)                                     | 149.95 (25.66)                                  | 0.000648632 |
| Average energy per walk cycle of dominant hip abduction velocity            | 50.6 (16.01)                                       | 59.65 (15.63)                                   | 0.028588101 |
| Average energy per walk cycle of dominant knee flexion velocity             | 211.66 (64.02)                                     | 284.34 (53.26)                                  | 1.40E-05    |
| Average energy per walk cycle of non-dominant hip flexion velocity          | 132.77 (57.35)                                     | 160.15 (29.48)                                  | 0.001067297 |
| Average energy per walk cycle of non-dominant hip abduction velocity        | 56.63 (27.44)                                      | 62.28 (16.69)                                   | 0.041416272 |
| Average energy per walk cycle of non-dominant knee flexion velocity         | 221.31 (89.05)                                     | 292.89 (53.72)                                  | 3.90E-05    |
| Number of Principal components to explain 90% variance                      | 7.49 (2.45)                                        | 5.8 (2.65)                                      | 0.016552015 |
| Walk complexity metric                                                      | 12.77 (3.32)                                       | 10.44 (3.69)                                    | 0.012014184 |
| Correlation between non-dominant hip abduction and non-dominant hip flexion | 0.12 (0.48)                                        | -0.15 (0.47)                                    | 0.038088284 |
| Correlation between non-dominant knee flexion and non-dominant hip flexion  | -0.49 (0.11)                                       | 0.02 (0.28)                                     | 2.57E-09    |

|                                                                              |                |               |             |
|------------------------------------------------------------------------------|----------------|---------------|-------------|
| Correlation between dominant hip flexion and non-dominant hip flexion        | -0.45 (0.1)    | -0.61 (0.08)  | 9.58E-08    |
| Correlation between dominant hip rotation and non-dominant hip flexion       | 0.2 (0.15)     | 0.09 (0.13)   | 0.002095939 |
| Correlation between non-dominant knee flexion and non-dominant hip abduction | -0.35 (0.43)   | -0.02 (0.26)  | 0.005490941 |
| Correlation between dominant hip flexion and non-dominant hip abduction      | -0.14 (0.28)   | 0.16 (0.34)   | 0.001793972 |
| Correlation between dominant hip flexion and non-dominant knee flexion       | 0.21 (0.16)    | 0.09 (0.19)   | 0.012014184 |
| Correlation between dominant knee flexion and non-dominant knee flexion      | -0.14 (0.18)   | 0.27 (0.12)   | 1.44E-08    |
| Correlation between dominant knee flexion and dominant hip flexion           | -0.57 (0.1)    | 0.06 (0.33)   | 3.18E-09    |
| Area of head movement on the transverse plane                                | 170.06 (77.29) | 39.38 (22.44) | 5.69E-10    |
| Variance of head movement in the frontal axis                                | 16.81 (8)      | 11.87 (8.07)  | 0.03917026  |
| Variance of head movement in the sideways axis                               | 12.88 (10.12)  | 2.92 (2.25)   | 5.38E-08    |

**Supplementary Table 3.** List of suit features from the 9HP task along with their mean and standard error values for the FA patients and control cohorts and p-value of the Kruskal-Wallis one-way ANOVA test between the cohorts. Data are presented as mean (standard deviation). Please note that there are 2 measurements per visit.

| Feature name                              | FA patients mean(std) (N=62 measurements) | Controls mean(std) (N=18 measurements) | p-value  |
|-------------------------------------------|-------------------------------------------|----------------------------------------|----------|
| Average velocity - Shoulder direction     | 13.87 (6.32)                              | 20.36 (8.7)                            | 1.17E-05 |
| Average velocity - Shoulder elevation     | 6.77 (2.58)                               | 17.22 (9.07)                           | 1.39E-15 |
| Average velocity - Shoulder rotation      | 12.75 (4.85)                              | 27.92 (8.73)                           | 7.81E-17 |
| Average velocity - Elbow flexion          | 14.93 (6.52)                              | 44.67 (32.16)                          | 8.68E-16 |
| Average velocity - Elbow pronation        | 14.62 (8.35)                              | 44.94 (38.09)                          | 4.40E-10 |
| Workspace volume                          | 2625.94 (1252.23)                         | 1423.11 (330.83)                       | 2.39E-10 |
| Workspace entropy                         | 0.17 (0.04)                               | 0.11 (0.02)                            | 1.48E-15 |
| Autocorrelation FWHM - shoulder direction | 293.53 (85.75)                            | 166 (61.54)                            | 3.75E-12 |
| Autocorrelation FWHM - shoulder elevation | 305.15 (111.99)                           | 227.03 (40.9)                          | 7.73E-06 |
| Autocorrelation FWHM - shoulder rotation  | 298.33 (93.8)                             | 190.65 (55.11)                         | 4.74E-10 |
| Autocorrelation FWHM - elbow flexion      | 238.07 (66.09)                            | 137.69 (36.75)                         | 7.40E-15 |

|                                                                           |                |                 |             |
|---------------------------------------------------------------------------|----------------|-----------------|-------------|
| Autocorrelation FWHM - elbow pronation                                    | 195.23 (72.24) | 121.71 (35.6)   | 5.57E-09    |
| 1st eigen spectrum values of the channel-delay cross-correlation matrix   | 32.19 (9.86)   | 42.42 (13.89)   | 2.08E-05    |
| 5th eigen spectrum values of the channel-delay cross-correlation matrix   | 22.66 (5.71)   | 33.17 (10.84)   | 1.39E-08    |
| 30th eigen spectrum values of the channel-delay cross-correlation matrix  | 6.44 (0.65)    | 8.23 (1.13)     | 3.33E-15    |
| 300th eigen spectrum values of the channel-delay cross-correlation matrix | 0.35 (0.11)    | 0.05 (0.06)     | 2.72E-19    |
| Average velocity - wrist                                                  | 6.95 (1.93)    | 10.87 (3.05)    | 6.46E-11    |
| Average power - shoulder direction                                        | 54.45 (26.18)  | 82.11 (35.7)    | 1.81E-06    |
| Average power - shoulder elevation                                        | 26.67 (10.16)  | 68.56 (37.92)   | 1.96E-15    |
| Average power - shoulder rotation                                         | 50.71 (21.69)  | 114.02 (37.38)  | 6.42E-17    |
| Average power - elbow flexion                                             | 59.49 (26.96)  | 187.25 (152.96) | 1.23E-15    |
| Average power - elbow pronation                                           | 58.95 (34.41)  | 195.46 (203.34) | 3.70E-10    |
| Area of head movement on the transverse plane                             | 53.81 (47.62)  | 8.69 (14.02)    | 1.36E-14    |
| Variability of wrist velocity                                             | 1.52 (0.55)    | 2.38 (0.66)     | 5.36E-10    |
| Number of Principal components to explain 90% variance                    | 7.29 (2.55)    | 4.43 (2)        | 6.05E-09    |
| Movement complexity metric                                                | 12.27 (3.1)    | 8.3 (2.68)      | 2.75E-10    |
| Variability of shoulder direction                                         | 10.36 (4.75)   | 15.12 (6.54)    | 1.66E-05    |
| Variability of shoulder elevation                                         | 4.99 (1.9)     | 12.71 (6.75)    | 1.63E-15    |
| Variability of shoulder flexion                                           | 9.47 (3.6)     | 20.78 (6.53)    | 6.85E-17    |
| Variability of elbow flexion                                              | 11.03 (4.87)   | 33.02 (24.62)   | 8.96E-16    |
| Variability of elbow pronation                                            | 10.72 (6.19)   | 33.17 (29.26)   | 6.07E-10    |
| Variability of neck flexion                                               | 1.56 (0.63)    | 2.44 (1.46)     | 0.000158969 |
| Variability of neck abduction                                             | 1.59 (0.64)    | 2.33 (0.75)     | 4.83E-07    |

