### **3) Development of reliable methodologies to measure clinical deficit and subtle neurological changes and correlation of functional changes to levels of expression of FXN protein and the epigenetic structure of the FXN gene (Part IV).**

A minimum of ten up to a maximum of 20 FRDA participants will be offered the opportunity to participate in Part IV. Up to 20 healthy volunteers (HV) will also participate in this part of the study.

Healthy volunteers will have an fMRI assessment during the execution of tasks, perform the SARA and SCAFI and scenarios wearing a body suit, perform eye movement tasks (optional) and perform a balance control task (optional). These assessments do not have to be performed on the same day. Including HV will provide us with a control comparison in individuals without a progressive deterioration.

Participants may be contacted by telephone and/or email or at their study visits (i.e FRDA participants participating in the interventional study) by the CI or delegates to inform them about the potential benefit and any risks associated with participation in this part of the study. fMRI contraindications will be detailed. Participants will be given the PIS and given as much time as they wish to read and ask questions. If the participant wishes to take part, informed consent will be given in writing prior to performing any study-related assessments. Participants will be assessed for fMRI contraindications during screening (including urine pregnancy test for women of child-bearing potential) prior to study start.

FRDA participants will undergo the assessments detailed below over the course of 2 days at the study start, 2 weeks ( $\pm 2$  days), 3 months ( $\pm 2$  weeks) and at 9-12 months ( $\pm 3$  months). In some cases if travel is difficult, participants will be offered overnight accommodation (at the Imperial CRF or private hospital accommodation).

1. Urine pregnancy test only for women of child-bearing potential (prior to fMRI).
2. Blood samples will be taken for:
  - FXN protein estimation by LC-MS/MS compared to the current dipstick assay (Mitosciences);
  - RNA-seq to identify informative biomarkers that might track FXN levels and

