13.2. Appendix 2: SCAFI

Timed walking test: 8m walk (8MW)

☐

test not performed, reason: \_\_\_\_\_

☐

proband unable to walk due to physical limitations

assistive device:

☐

none

☐

one cane /crutches

☐

orthosis

☐

two

cane /crutches

☐

wheeled walker

Did situations arise that necessitated repetition of a trial ( e.g. proband fell, external interference during walking, examiner forgot to start/ reset stopwatch) ?

\_\_\_\_\_

Other factors that might have affected performance ?

\_\_\_\_\_

Times are only given for two successfully completed trials.

|                   |                      |          |                   |                      |          |
|-------------------|----------------------|----------|-------------------|----------------------|----------|
| Trial 1 (0.1 sec) |  | (8MW_T1) | Trial 2 (0.1 sec) |  | (8MW_T2) |
|-------------------|----------------------|----------|-------------------|----------------------|----------|

Timed dexterity test: 9-hole peg test (9HPT)

☐

test not performed, reason: \_\_\_\_\_

☐

proband unable to perform test due to physical limitations

Did situations arise that necessitated repetition of a trial ( e.g. pegboard not sufficiently secured on the table, external interference, examiner forgot to start/ reset stopwatch/ turn pegboard)? \_\_\_\_\_

Other factors that might have affected performance ? \_\_\_\_\_

Times are only given for two successfully completed trials for each hand

| DOMINANT HAND                                                                                                                               | NON-DOMINANT HAND                                                                                                                           |
|---------------------------------------------------------------------------------------------------------------------------------------------|---------------------------------------------------------------------------------------------------------------------------------------------|
| Right 
Left  | Right 
Left  |

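### Supplementary Table 3 prints p-values that its stated N of 62 v 18 cannot give, and Supplementary Tables 2 and 3 both test repeated measurements as if independent, so FRDA-v-control separation is overstated

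*Protocol*

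**What the plan says.** Supplementary Tables 2 (8-metre walk) and 3 (9-hole peg test) list suit features with a mean and spread per cohort and a p-value. The Table 3 caption names its source as the "Kruskal-Wallis one-way ANOVA test between the cohorts. Data are presented as mean (standard deviation). Please note that there are 2 measurements per visit". Table 3 heads its columns "FA patients mean(std) (N=62 measurements") and "Controls mean(std) (N=18 measurements"); Table 2 states the same N. Both captions add "Please note that there are 2 measurements per visit". Neither mentions averaging within a person or any allowance for clustering, and neither gives the number of people.

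The protocol supplies three further facts:
- The SCAFI form (Appendix 2) says of the peg test: "Times are only given for two successfully completed trials for each hand".
- Section 4.1 limits the cohorts of Part IV: "A minimum of ten up to a maximum of 20 FRDA participants will be offered the opportunity to participate in Part IV", and "Up to 20 healthy volunteers (HV) will also participate in this part of the study".
- Sections 4.1 and 12.2 schedule each FRDA participant at four time points: start, 2 weeks, 3 months and 9-12 months.

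**The concern.** Two separate defects are present.

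The first is arithmetic. A rank test on two groups of fixed size has a smallest attainable p, reached when the groups do not overlap at all. If printed values lie below it, then the stated N, the stated test and the printed p-values cannot all be correct.

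The second is the unit of analysis. Kruskal-Wallis assumes independent observations. Two trials at one visit, both hands of one person and several visits by one person are correlated. Counting each as a new observation makes p too small.

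At stake is the cross-sectional claim that suit features separate FRDA patients from controls. Section 4.2 relies on healthy volunteers as the normal baseline for new clinical scales, and Section 7.2 foresees classifiers built on these recordings.

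**Working it through.** **Test statistic.** For two groups without ties, with N = n1 + n2, H = (U − n1·n2/2)² / [n1·n2·(N+1)/12], and p is the upper tail of chi-square with 1 df. At complete separation U = 0, so the maximum H is 3·n1·n2/(N+1).

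**Step 1: reproduce Table 2 at its stated N.** At 62 v 18, n1·n2/2 = 558 and the denominator is 62·18·81/12 = 7533. U = 340 gives H = 218²/7533 = 6.309 and p = 0.012014184, a value printed twice in Table 2. Matching every attainable value to the table reproduces 29 of 31 rows to the printed digits; 6.44E-07 and 0.03917026 do not match. Among all pairs with n1 from 8 to 199 and n2 from 8 to 59, the next best matches 16 rows. Table 2 was therefore computed with the plain chi-square form, each measurement counted as one independent value.

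**Step 2: the floor for Table 3 at its stated N.** Maximum H = 3·62·18/81 = 41.33, so the smallest p is 1.28E-10. Sixteen of the 33 Table 3 values are below it, from 6.46E-11 down to 2.72E-19. No Table 2 value is.

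Other forms of the test at 62 v 18:

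| Form | Smallest p | Table 3 values below |
|---|---|---|
| Chi-square (fits Table 2) | 1.28E-10 | 16 |
| One-sided | 6.4E-11 | 15 |
| Exact two-sided permutation | 5.6E-18 | 1 |
| Extreme ties | 6.2E-19 | 1 |

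**Step 3: which N fits Table 3.** Over the same range of pairs, 132 v 36 reproduces 31 of 33 rows (2.39E-10 and 6.05E-09 do not match). The next best pair reproduces 15, and 62 v 18 reproduces none. At 132 v 36, n1·n2/2 = 2376 and the denominator is 132·36·169/12 = 66924. U = 53 gives H = 2323²/66924 = 80.63 and p = 2.72E-19; U = 1399 gives H = 977²/66924 = 14.263 and p = 0.000158969. These are the smallest and largest printed values. The floor at this N is 4.1E-20, so every printed value becomes possible. With two trials for each of two hands, 132/4 = 33 FRDA visits and 36/4 = 9 control visits.

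**Step 4: repeats.** In Table 2, 62/2 = 31 FRDA visits and 18/2 = 9 control visits. With at most 20 FRDA participants, at least 31 − 20 = 11 FRDA visits are repeats. With 9 control visits there are at most 9 controls.

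**Step 5: size of the effect of paired trials in Table 2.** If the two trials at a visit were fully correlated, H would be about halved. A feature then needs a printed H of at least 2·3.841 = 7.683, that is a printed p of at most 0.00557, to stay at p ≤ 0.05. Eleven of 31 rows exceed that limit. One row is borderline (0.005490941, H about 7.71): the exact 31 v 9 ratio, 20.41/41.33 = 0.494, gives 7.71·0.494 = 3.81, just under 3.841. Repeat visits are not included here.

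**Step 6: what would probably survive.** The matched U values imply AUC = 1 − U/(n1·n2) of 0.65-0.98 in Table 2 and 0.71-0.99 in Table 3. With AUC held fixed and one value per person, H = 3·n1·n2·(2·AUC − 1)²/(N+1). The head counts are assumptions.

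| People (FRDA v control) | Table 2, p<0.05 | Table 3, p<0.05 |
|---|---|---|
| 10 v 9 | 14 of 31 | 27 of 33 |
| 20 v 9 | 18 of 31 | 32 of 33 |

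**The case against.** The strongest reply is that these tables belong to a results supplement and not to the trial plan. They call their units measurements and disclose two per visit. No eligibility rule, sample size, endpoint or decision rule rests on them. All of that stands, and it limits the severity. It does not repair a stated N that contradicts the printed p-values, or a test applied to correlated records.

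Further points that stand:
- The count of 16 belongs to the chi-square form. Under an exact permutation test only 2.72E-19 would be impossible. The Table 2 match points to the chi-square form, and no form examined makes every Table 3 value possible at 62 v 18.
- Two trials for each of two hands is an inference from the fit and the peg-test form. It implies 33 FRDA visits against 31 in Table 2, and the documents do not explain the difference.
- Participant numbers are not stated.

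A reader might infer more than the documents support:
- *That the wrong N inflates the evidence.* It does not. It shows misreporting in Table 3; the overstatement comes from ignored clustering, in both tables.
- *That the distance below a participant-level floor measures the inflation.* At 20 v 9 people the floor is 2.2E-05, and 32 of 33 Table 3 values lie below it. That reflects ranking few people; Step 6 shows that most of those features could stay significant.
- *That a false discovery rate over the 64 listed features is required.* The number of features tested is not given, so that family may be wrong.
- *That the prediction results fail too.* The captions of Supplementary Figs. 3 and 8 describe leave-one-subject-out cross-validation, which already holds out whole people.

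**Conclusion.** The point holds as two distinct errors. For Table 3, the printed N and the stated two measurements per visit are wrong; the p-values correspond to 132 v 36 values. For both tables, the p-values are too small because repeated measurements were tested as independent.

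The figure of 11 of 31 Table 2 features is an upper bound for the effect of paired trials alone, and it uses the approximate halving of H. The minimum of 11 repeat FRDA visits assumes that the reported cohort kept to the Part IV cap of 20. The survival counts assume that the AUCs would not change with one value per person.

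FRDA-v-control separation is overstated, but the documents do not show that it is absent. The interventional FXN endpoint and the leave-one-subject-out prediction analyses are not affected. Severity: a moderate correction of reported results.

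**What to change.** 1. Correct the N in the Table 3 header and the measurements-per-visit statement in its caption, and say what one measurement is (trial, hand, visit).
2. State the number of people and visits per cohort in both tables.
3. Recompute the FRDA-v-control p-values in both tables with the participant as unit: either one value per person (for example the mean over trials, hands and visits, or the first visit only), or a mixed model or permutation test that keeps each person's records together.

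The cost is a re-analysis of existing data, with no new collection. The downside is larger p-values and fewer listed features, chiefly among the weaker walking features in Table 2.
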